## Study objectives

The main and primary “key” objective pursued in this clinical trial is to (1) identify the clinical potential of the multitarget cortical stimulation by comparing the effect of three tDCS interventions (anterior cerebellar lobe stimulation, dorsolateral prefrontal stimulation and the combination thereof) driving clinical improvements of upper limb motor function in stroke patients, as assessed by the Fugl-Meyer Assessment (FMA). We specifically hypothesize (key hypothesis of the study) that combined stimulation of the former two cerebral sites will enhance clinical recovery compared to sham stimulation and also to the stimulation of either site (anterior cerebellar or dorsolateral prefrontal) in isolation.

The secondary objectives of our clinical trial are: (2) to evaluate the influence of such interventions on specific cognitive and motor processes sensitive to the contribution of the modulated targets, i.e., via an impact on sustained attention and cognitive control (dorsolateral prefrontal tDCS) or motor adaptation skills (anterior cerebellar tDCS); (3) to explore whether clinical improvements are induced by isolated interventions or if their combination can be associated to the normalization of neurophysiological outcome measures (increased local and/or inter-areal synchronization or changes of abnormal neural states, taken as proxies of enduring adaptive plasticity); finally, (4) to identify biomarkers (clinical and cognitive scores, neuroimaging features, and electrophysiological measures and tDCS current distribution modelled parameters) associated to the severity of motor impairments and their improvement following stimulation.

## Material and methods

### Study settings

This trial will be conducted in the *Hospital Universitari Joan XXIII*, Tarragona, Spain. All interventions and assessments will be carried out in the Rehabilitation and Physical medicine department of this hospital. MRI acquisitions will be performed in the Radiology and Nuclear medicine department in this same clinical institution. An IRB protocol in accordance with the Declaration of Helsinki covering all its procedures and interventions with the registration number: 077/2021 (version: V.1_06/05/) has been officially approved on June 27th 2021 by the local ethics committee of the *Institut d’investigació sanitària Pere Virgili* (IISPV, Tarragona, Spain).

### Study design

The present clinical protocol (hereafter entitled *E-Brain*) is designed as a double-blind, parallel, sham-controlled, randomized clinical trial.

### Study summary

Participants will be randomly assigned to one out of the following 4 groups, GROUP 1: (ipsi-DLPFC) anodal tDCS stimulation of the ipsilesional dorsolateral prefrontal cortex; GROUP 2: (contra-CEREB): anodal stimulation of the contralesional cerebellar cortex (anterior lobe); GROUP 3: (ipsi-DLPFC + contra-CEREB) combined anodal stimulation of the ipsilesional DLPFC and the anodal contralesional cerebellar cortex; and GROUP 4: (SHAM tDCS) consisting in sham/placebo stimulation (see Fig. 1A).

**Fig. 1 Fig1:**
[figure not shown]
**A** Flow diagram of the study design. The diagram presents a weekly calendar where W0 denotes the baseline assessment and the interventional starting point for a representative subject. contra-CEREB: anodal contralesional anterior cerebellar lobe stimulation, ipsi-DLPFC + contra-CEREB: anodal ipsilesional DLPFC tDCS combined with anodal contralesional anterior cerebellar lobe simultaneous tDCS, ipsi-DLPFC: anodal ipsilesional dorsolateral prefrontal tDCS, SHAM: sham tDCS stimulation, W0: week 0 (baseline assessment), W1-2: weeks 1 and 2 (interventional weeks were the 10 days tDCS treatment is executed), W3: week 3 (post-intervention assessment), W7: week 7 (follow-up assessment). **B** Standard protocol items: recommendations for interventional trials (Supplementary file 1). Schematic summary and milestones for enrolment, tDCS treatment, and assessments across the study time-line

For all groups, a daily tDCS session will be administrated for 10 consecutive days, with a regime of 5 sessions per week for 2 weeks (Monday to Friday). A conventional clinical magnetic resonance imaging (MRI, 3D-T1) recorded between the 1st and 3rd month after the stroke event will be retrieved from the participant’s medical history or recorded at the the Hospital Universitari Joan XXIII, Tarragona (Spain) within 2 weeks prior to the trial onset. Clinical scales or scores, behavioral computer-based tasks, and electroencephalography (EEG) evaluations will be carried out at 3-time points or milestones: (I) Baseline assessment: 72–96 h (2–3 days) before the onset of the tDCS regime; (II) Post-tDCS assessment: 72–96 h (2–3 days) after the end of the tDCS regime; and (III) Follow-up assessment: 30 days after the end of the tDCS regime. Across sessions, all evaluations will be carried out under identical conditions (see Fig. 1A, B). The current protocol E-Brain follows the SPIRIT recommendations (see Additional file 1).

### Participant recruitment

Participants will be enrolled through the Rehabilitation and Physical Medicine department of the *Hospital Universitari Joan XXIII* in Tarragona, Spain. Only those patients attending the rehabilitation service enrolled in an active rehabilitation program (hereafter referred to as a “live” rehabilitation program) will be assessed for eligibility. An experienced licensed medical doctor ([name]) working for the protocol will initially screen potential participants fulfilling eligibility criteria. Following verification of inclusion criteria, participants willing to participate will be presented with the details of the protocol and asked to sign a consent form to be officially included in the study.

### Inclusion criteria

 The following inclusion criteria have been established as to be fulfilled by potential participants: (1) to have received a diagnosis of supratentorial ischemic or hemorrhagic unilateral stroke supplied by the middle cerebral artery (i.e., encompassing frontal–temporal-parietal regions); (2) to be enrolled in a “live” rehabilitation program in the Rehabilitation and Physical Medicine department of our institution; (3) to be between 18 and 85 years old; (4) to have suffered a stroke within 4 and 12 months prior to enrollment; (5) to have signed the informed consent form.

### Non-inclusion criteria

Stroke participants presenting at least one of the following criteria will not be able to participate in our study: (1) unstable medical condition (e.g., affected by infections, with assisted ventilation, having suffered or actively suffering epilepsy or recurrent seizures, untreated psychiatric disorders, or being under an active treatment with sedative drugs); (2) participants presenting contraindications to tDCS according to the most current international NIBS safety guidelines [10]; (3) participants presenting cognitive impairments-such as severe aphasia or neuropsychiatric deficits-limiting their comprehension and their ability to follow instructions. The verification of non-inclusion criteria will be documented by means of an in-house screening questionnaire.

### Exit criteria

Patients will be dropped out from the study if: (1) they manifest, at any time and without the need to provide any explanation, their willingness to stop their participation in the clinical trial; (2) they are not compliant with the procedures of the study; (2) they experience severe discomfort or annoyance during their participation (i.e., insomnia, headache, etc.); or (3) in case of unexpected events that incapacitate patients to continue in the study. Data collected until a participant is officially considered a 'drop-out' will be included in analyses, hence not withdrawn from the study.

### Sociodemographic data

During the baseline assessment, patients will be asked to complete to the best of their knowledge and ability a questionnaire including the following information: (1) age and sex; (2) stroke features (hemisphere affected, localization, stroke type, time since stroke event, pre-morbid conditions); (3) socio-educational information (marital status, academic level, occupation, leisure hobbies, technology usage, sport practice, smoking, alcohol or drug usage and ongoing medication); (4) past and ongoing stroke rehabilitation program (post-stroke-onset time, types of ongoing and completed programs, frequency, intensity, and periodicity). Stroke lesion features, details of the clinical history, and any missing medical information required to complete the above-mentioned questionnaire will be verified and/or completed by a legally authorized member of the medical team collaborating with the protocol (co-author [name]).

Additionally, the Edinburgh manual dexterity scale and the Beck’s inventory will be administered to characterize the patient’s laterality and assess the participant’s mood, respectively.

### Sample size

The current study is designed as a pilot clinical trial aiming to assess the effects of an isolated monofocal (single cortical site stimulation, i.e., either the dorsolateral prefrontal cortex or the anterior cerebellar lobe) or combined multifocal (simultaneous stimulation of the two former sites) multiday tDCS intervention using a high-density array of electrodes. Given the exploratory character of our study, no power analysis to estimate sample size was required by the local IRB committee. Instead, following standardized guidelines for experimental clinical trials, we considered the number of participants included in past similar exploratory tDCS studies warranting sufficient statistical power [35] and ensuring recruitment feasibility, and we concluded the need to include at least *n* = 15 patients in each of our 4 tDCS treatment groups.

### Randomization and blinding

The study will include *n* = 60 patients with chronic MCA stroke, randomly assigned to one of the 4 experimental groups indicated above (ipsi-DLPFC, contra-CEREB, ipsi-DLPFC + contra-CEREB, or SHAM tDCS). A patient randomization algorithm (*MinimPy* software running in *Python environment*, https://sourceforge.net/projects/minimpy/) counterbalancing groups by sex (Woman/Male), age (− 65 years/ + 65 years) and stroke type (ischemic/hemorrhagic) will ensure equivalence for these three variables across the 4 experimental groups. The biased coin method is an algorithm implementing a biased coin minimization algorithm (base probability: 1, allocation ratio 1:1:1:1) [36] for sequential dynamic allocation, in which each new allocation is influenced by the current state of balance across delivered treatments [37].

An independent co-investigator not involved in the recruitment/enrollment of patients, tDCS application or in clinical evaluation will be in charge of patient randomization and condition/group allocation. The groups of patients associated with the four randomized tDCS conditions will be assigned a letter-coded name (Groups A, B, C, or D) providing no clue with regard to the ultimately delivered tDCS strategy. This same code will be used at all times for patient allocation and only an independent co-investigator in charge of randomization/allocation activities will be able to associate each of the codes (A, B, C, and D) to a specific tDCS condition (aka treatment group). Once a patient will be randomly assigned to a condition/treatment group, its code (A, B, C, or D) will be communicated to a team member in charge of stimulation which will simply deliver it blindly in a non-identifiable manner. To search for the potential influence of placebo or nocebo effects, investigators will debrief at the end of the follow-up, with patients and ask them to guess which stimulation group they believed they had been allocated to (allocation perception).

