In order to characterize the electrophysiological EEG effects induced by our interventions, we will first explore correlations with behavioral data and biomarkers of recovery. First, power spectral density (PSD) changes for each frequency band will be compared between stimulation groups using two-tailed ANOVA (*P* = 0.05), with “TIME” as the within-subject factor and “GROUP” as the between-subject factor. To correct for multiple comparisons, non-parametric cluster-based permutation statistics with Montecarlo sampling (1000 permutations) will be applied, allowing the examination of global effects across all electrodes while controlling for multiple comparisons at the sensor level, without the need of prior assumptions about effect location. Finally, connectivity (imaginary part of coherence measures) and entropy effects (complexity of temporal dynamics) of the electrophysiological response will be also explored. The same statistical procedure as for PSD exploration applying repeated measures ANOVA with non-parametric cluster-based permutation statistics and MonteCarlo sampling (1000 permutation) will be used, with “TIME” as within factor, and “GROUP” as between factor. Individually averaged connectivity and entropy values (total averages) and individual topographical maps at the electrode level will be examined to detect specific regions sensible to the tDCS intervention.

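### The EEG analyses leave out the three factors used for minimisation; if those factors predict the tested EEG quantity, the nominal 5% tests are conservative and lose some power

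*Protocol article*

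**What the plan says.** **Allocation** (Protocol article, Randomization and blinding). "The study will include *n* = 60 patients with chronic MCA stroke", and the Sample size section asks for "at least *n* = 15 patients in each of our 4 tDCS treatment groups". Patients are allocated by a "biased coin minimization algorithm (base probability: 1, allocation ratio 1:1:1:1"). The balancing factors are sex, age cut at 65 years, and stroke type. The article says that balancing on sex, age "and stroke type (ischemic/hemorrhagic) will ensure equivalence for these three variables across the 4 experimental groups". The scheme is sequential, "in which each new allocation is influenced by the current state of balance across delivered treatments". With base probability 1 the favoured arm is always taken, so chance enters only at ties.

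**EEG analysis** (Protocol article, Statistical analyses). Spectral power changes are compared between arms "using two-tailed ANOVA (*P* = 0.05"), with TIME within and GROUP between patients. For multiplicity over electrodes, "non-parametric cluster-based permutation statistics with Montecarlo sampling (1000 permutations) will be applied". Connectivity and entropy follow suit: "The same statistical procedure as for PSD exploration applying repeated measures ANOVA with non-parametric cluster-based permutation statistics".

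Sex, age group and stroke type do not appear in this EEG model. The section does not say what is permuted, or whether the permutation is tied to the allocation.

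**The concern.** Minimisation makes the arms much more alike on the three factors than chance would. If those factors carry information about the EEG variable, the arm means vary less under no effect than an unadjusted test assumes. The factor variance still sits in the within-arm error term, or in the shuffled reference distribution, but hardly at all in the observed differences between arms. The test then rejects less often than 5% under the null, and some of the precision that the allocation bought is not used.

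What is at stake is power for secondary mechanistic outcomes with 15 patients per arm. The Discussion presents the balancing as a safeguard against patient differences that could make behavioural and EEG evidence less reliable. Leaving the same factors out of the EEG model does not fit well with that reasoning.

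**Working it through.** **Inputs from the article:** N = 60 = 4 x 15; four arms 1:1:1:1; minimisation with probability 1 on three two-level factors; nominal level 0.05. The article gives no power calculation or EEG variance, so apart from the nominal 0.05 there is no figure of the plan to reproduce.

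**Assumed:** R2, the share of variance of the tested EEG quantity explained by the three factors together (range 0 to 30% shown, equal contributions); factor prevalences of 45%, 50% and 20%; ties broken at random.

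**Step 1: how much minimisation tightens balance.** In 4000 simulated allocations, the variance of the between-arm difference in the combined factor score was 0.0112 under minimisation and 0.1368 under free shuffling. The ratio is 0.0112 / 0.1368 = 0.082.

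**Step 2: approximate size.** The between-arm variance shrinks by r = (1 - R2) + 0.082 x R2. The 5% critical value of F(3, 56) is 2.769. The approximate true size is therefore P[F(3, 56) > 2.769 / r]. For R2 = 10%: r = 0.90 + 0.008 = 0.908; 2.769 / 0.908 = 3.05; tail probability 3.6%.

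**Step 3: simulated size.** One EEG variable, 5000 trials per R2, F statistic referred to 999 free label permutations (standard error about 0.3 points near 5%):

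| R2 | r | Approximate size | Simulated size |
|---|---|---|---|
| 0% | 1.000 | 5.0% | 5.0% |
| 2% | 0.982 | 4.7% | 4.8% |
| 5% | 0.954 | 4.3% | 4.2% |
| 10% | 0.908 | 3.6% | 3.5% |
| 20% | 0.816 | 2.4% | 2.6% |
| 30% | 0.725 | 1.5% | 1.5% |

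The maximum F over 8 correlated electrodes, as a stand-in for the cluster statistic (3000 trials), gave 4.8%, 3.0% and 0.7% at R2 of 0, 10 and 30%.

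**Step 4: is permutation the cause?** An ordinary parametric F test without the factors (4000 trials) gave 4.3%, 3.9% and 1.5% at R2 of 0, 10 and 30%. With the three factors added it gave 4.3%, 5.3% and 5.8%. The loss of size therefore comes from omitting the factors and does not depend on permutation.

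**Step 5: which contrast is affected?** With three time points and factors that explain 30% of EEG level but none of its change (3000 trials), the test of change from baseline to post-tDCS, taken as the TIME x GROUP contrast, had size 5.1%. The GROUP main effect had size 0.9%. Effects on level cancel in the change.

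**Step 6: do the remedies work?** Free permutation against Freedman-Lane residual permutation, 499 draws. Size from 2500 trials (standard error about 0.4 points); power from 1500 trials (about 1 point) for a shift of 1 SD in one arm:

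| R2 | Size, free | Size, Freedman-Lane | Power, free | Power, Freedman-Lane |
|---|---|---|---|---|
| 0% | 5.1% | 5.4% | 0.78 | 0.78 |
| 5% | 3.4% | 4.4% | 0.80 | 0.82 |
| 10% | 3.5% | 5.0% | 0.76 | 0.80 |
| 20% | 2.9% | 5.8% | 0.78 | 0.87 |
| 30% | 0.9% | 4.6% | 0.77 | 0.91 |

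Re-randomising through the minimisation (2000 trials, 399 draws) gave sizes of 4.3%, 4.5% and 4.6% at R2 of 0, 10 and 30%. Its power for a 0.9 SD shift was 0.651 against 0.669 for free permutation at R2 = 10%, and 0.765 against 0.655 at R2 = 30%. It corrects the reference distribution but leaves the factor variance in the error term, so it gains less than adjustment does.

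**The case against.** **The permutation scheme is not described.** A reader might infer that EEG p-values come from shuffling patients freely over the arms, that this scheme is invalid in itself, and that all the 5% EEG tests are therefore conservative. The documents do not support that. They give the procedure and the number of draws, not what is shuffled, and a condensed article may leave this to a fuller document. This objection stands. What the article does fix is the model terms, TIME and GROUP, and the point rests on those.

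**The main treatment contrast may be unaffected.** The tDCS effect lies in TIME x GROUP, where factor effects on EEG level cancel (step 5). This stands too: for that contrast only factors that predict EEG change matter.

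**The size is assumed.** No R2 is given. At 0% there is no loss, and at 5% it is under one percentage point of size.

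**Little power is lost against simple randomisation.** A 1 SD shift in one arm of 15 has noncentrality 15 x (0.75² + 3 x 0.25²) = 11.25, which gives power 0.783 on 3 and 56 degrees of freedom. The unadjusted test after minimisation stays close to that at every R2 examined. So the loss is a gain forgone relative to an adjusted analysis, about 2 to 4 points at R2 of 5 to 10%.

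**Freedman-Lane also permutes freely.** In principle it includes arrangements that the minimisation could not produce. In simulation its size was nevertheless close to 5% (4.4 to 5.8%). Re-randomisation is the alternative for anyone who wants the reference set to match the design.

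**Conclusion.** The point holds in a conditional form. The trial allocates by near-deterministic minimisation on three factors, and the EEG model as written omits them. Where they predict the tested quantity, unadjusted tests are conservative: about 4.2, 3.5 and 2.6% in place of 5% at assumed R2 of 5, 10 and 20%. At R2 of 0 the size is 5.0%.

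The R2 values and prevalences are assumptions, and the simulated permutation is unrestricted because the article states no restriction. The error goes one way only: effects may be missed, but false positives are not inflated. The outcomes are secondary and exploratory, in a pilot without a power calculation, so this is a minor point and a nearly free improvement. It is not a flaw in validity.

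**What to change.** In Statistical analyses, for the EEG outcomes:

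- State what is permuted for each contrast.
- Adjust EEG change from baseline (for TIME x GROUP) and EEG level (for the GROUP main effect) for sex, age group and stroke type, and permute the residuals by Freedman-Lane within the cluster-based test. Alternatively, generate the reference distribution by re-running the minimisation with the patients' actual entry order and factor values. Adjustment is the better choice for power.
- Apply the same scheme to spectral power, connectivity and entropy.

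The cost is three degrees of freedom and a few lines of code, with no new data. Trial status reports recruitment still under way with 11 completers, so the change can be fixed before unblinding.

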### Interventions

#### tDCS electrode montage

Prior to the design of the present clinical Trial, we optimized a HD-tDCS electrode montage solution to be able to target simultaneously the DLPFC and the anterior lobe of the cerebellum using an 8-channel tDCS (Starstim, NE) equipment. The optimized computational model was generated in MATLAB (R2019a, Mathworks, USA) and SimNIBS 3.2.3 [38], an open-source package for the simulation of non-invasive brain stimulation electrical field based on participant’s MRI volumes using a standard head/brain volume MNI152 (version 2009a) as template (available through the open dataset of SimNIBS). The “lead field matrix” computation defining the scalp localization of tDCS electrodes was based on the 10/20 EEG system and $${\mathrm{\pi cm}}^{2}$$ predefined tDCS electrode size. The MNI152 standard head model was reconstructed with the *headreco* routine relying on SPM12 and CAT12 for segmentation. Isotropic conductivity values were set as follows (in S/m) based on previous studies [39, 40]: WM 0.126, GM 0.275, CSF 1.654, bone 0.010, scalp 0.465, eye balls 0.500, compact bone 0.008, spongy bone 0.025, blood 0.600, muscle 0.160. The selected electrode solution (in terms of electric field focality, intensity, and electrode compatibility with an 8-channel tDCS *NE Starstim* device) was obtained by optimizing the electrode positions of each cerebral target separately (ipsi-DLPFC and contra-CEREB) and merging these solutions in a simulation of combined stimulation scenario (ipsi-DLPFC + contra-CEREB).

For an optimal simulation of the left (ipsilateral) DLPFC (MNI *x* =  − 39 *y* = 34 *z* = 37 to influence the Dorsal Attentional Network, DAN), we obtained the best solution limiting the total number of electrodes to 3. Additionally, given technical limitations of our ISO and CE certified tDCS device and to warrant patient safety, a total maximal current of 4 mA and a maximal individual electrode current of 2 mA were used. Ipsilesional prefrontal target coordinates (ipsi-DLPFC) were defined on the basis of previous studies ensuring a high E-field impact in Brodmann area 46 (BA46) [41]. For the computation of the optimal right contralateral cerebellum stimulation site (MNI *x* =  24 *y* =  − 66 *z* =  − 40) and to optimally impact its anterior lobe (contra-CEREB), the best solution was found with a total number of 5 scalp electrodes, a maximum current of 4 mA, and maximum individual electrode current of 2 mA[42]. We also modified the E-field *direction* controlling field strength at the target instead of a tangential orientation. Importantly, to favor spatial selectivity and avoid electrode dispersion, the contralesional temporal cortex (MNI *x* =  53 *y* =  − 6 *z* =  − 41, hence contralateral to the stimulated DLPFC) and the ipsilesional anterior cerebellar lobe (MNI *X* = -9 *Y* =  − 88 *Z* =  − 44, contralateral to the stimulated CEREB) were defined as “avoidance” regions which tDCS montages excluded from being impacted.

Current evidence from in vitro and in vivo studies has demonstrated that tDCS field strength close to 0.25 V/m are sufficient to alter neuronal excitability via modulation of its resting-state potential [9, 43, 44]. Due to the dual-site experimental approach tested in our study (simultaneous stimulation of two sites, cerebellar and prefrontal for the combined tDCS condition) and considering a maximum of 4 mA injected current with high-density electrode montages (current density up to 0.63 mA/$${\mathrm{cm}}^{2}$$), the optimization algorithm generated assuming a left hemisphere stroke (right ipsi-DLPFC and left contra-CEREB stimulation), suggested 0.25 V/m simultaneously to both targets. This intensity was also retained to avoid possible side effects and warrant the safety/tolerability of our electrode montage. The “flipped version” of the former montage, hence assuming a right hemisphere stroke (right ipsi-DLPFC and the left contra-CEREB stimulation) was also simulated and delivered the same optimized electrode solution (see Fig. 2 for details).

